## 8.3. Safety Assessments

The definitions of an AE and an SAE and MAAE can be found in Table 8.4.1.

Planned time points for all safety assessments are provided in the Flow-Chart. Unscheduled clinical laboratory measurements may be obtained at any time during the study to assess any perceived safety issues.

A clinical assessment, including medical history, will be performed on all participants at his/her first visit to establish a baseline. Significant medical history and observations from any physical examination, if performed, will be documented in the eCRF.

Acute reactions within the first 15 minutes will be assessed and documented in the eCRF.

AEs will be reported by the participant (or, when appropriate, by a caregiver, surrogate, or the participant's legally authorized representative).

The investigator and any qualified designees are responsible for detecting, documenting, and recording events that meet the definition of an AE or SAE and remain responsible to pursue and obtain adequate information both to determine the outcome and to assess whether the event meets the criteria for classification as an SAE or caused the participant to discontinue the study intervention.

AEs will be documented in the eCRF for each visit as determined in the Flowchart.

#### 8.4. Adverse Events (AEs), Serious Adverse Events (SAEs), and Other Safety Reporting

The definitions of the EU Directive 2001/20/EC Article 2 based on the principles of GCP and EU guidance ENTR/CT 3 apply to this trial protocol, when required local requirements should also apply.

**Table 8.4.1: Definitions of Adverse Events**

| TERM                                                         | DEFINITION                                                                                                                                                                                                                                                                                                                                                           |
|--------------------------------------------------------------|----------------------------------------------------------------------------------------------------------------------------------------------------------------------------------------------------------------------------------------------------------------------------------------------------------------------------------------------------------------------|
| Adverse Event (AE)                                    | Any untoward medical occurrence in a patient or clinical trial participant, which does not necessarily have a causal relationship with the research procedures or the investigational medicinal product (IMP).                                                                                                                                                       |
| Adverse Reaction (AR)                                 | Any untoward and unintended responses to an IMP related to any dose administered.                                                                                                                                                                                                                                                                                    |
| Serious Adverse Event or Reaction (SAE/SAR)*          | Any AE/AR that, at any dose, results in: 
 
- death;
 
- a life-threatening AE;
 
- hospitalization or prolongation of existing hospitalization;
 
- a persistent or significant disability or incapacity;
 
- a congenital anomaly/birth defect;
 
- an "important medical event"
 
 |
| Suspected Unexpected Serious Adverse Reaction (SUSAR) | An unexpected adverse reaction is an AR of which the nature, outcome, frequency or severity is not consistent with the applicable Reference Safety Information (RSI): SmPC or Investigator's Brochure (IB).                                                                                                                                                          |
| Medically Attended Adverse Events (MAAEs)             | Adverse events with medically-attended visits that were not routine visits for physical examination or vaccination, such as visits for hospitalization, an emergency room visit, or an otherwise unscheduled visit to or from medical personnel (medical doctor) for any reason                                                                                      |
| New fact**                                            | Any safety data that could modify significantly the evaluation of the benefit/risk ratio of the IMP or the clinical trial, likely to affect the safety of participants or that could modify the IMP administration, the trial documentation or the conduct of the trial, or to suspend, interrupt or modify the protocol or similar trials.                          |

*\* EXCEPTIONS: the following events are not considered as SAE requiring immediate reporting to the sponsor:*

*-the participant is formally admitted to a hospital for medical reasons with no seriousness criterion and does not require overnight hospitalization*

*-elective or previously scheduled surgery or medical treatment;  
-hospitalization for social or administrative reasons;  
-pre-existing diseases or present conditions detected prior to start of study drug administration and which do not worsen.*

*\*\*Example: a SAE which could be associated with the trial procedures and which could modify the conduct of the trial, a significant hazard to the subject population such as lack of efficacy of an IMP used for the treatment of a life-threatening disease, recommendations of the data safety monitoring board, if any, where relevant for the safety of subjects.*

#### **8.4.1. Time period and frequency for collecting and reporting AE and SAE information**

- All AEs and SAEs will be collected from the signing of the informed consent form (ICF) until the follow-up visit at the time points specified in the Flowchart.
- All AEs and SAEs that are related to investigational products will be recorded from the time of ICF signing to end of study or early study discontinuation.
- Any clinically relevant event that occurs between signing of the ICF and the first vaccination will be collected and reported as pre-existing medical condition.
- All information on AEs (non-serious and serious) and pregnancies should be recorded on the appropriate eCRF (eCRF completion will be detailed into eCRF user manual).
- All AEs will be monitored until resolution or clinical stabilization.
- SAE information will be transmitted using a SAE form. The form should be reviewed and signed by an investigator and must be transmitted within 24 hours from initiation of SAE.
- All events that meet the definition of a SAE will be reported as SAEs, regardless of whether they are protocol-specific assessments.

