| Safety                                                                                                                                                                                                                  |                                                                                                                                                                                                                                                                                                                                                                                                                                                                                                          |
| To evaluate the safety of a dose of COMIRNATY in subjects that received a previous single dose of VAXZEVRIA.                                                                                                                   | 
- Solicited local and systemic adverse events (AEs) for 7 days after vaccine
 
- Unsolicited local and systemic adverse events (AEs) for 28 days after vaccine (Two days per week)
 
- Serious adverse events (SAEs) throughout the study (from randomization until end of the study).
 
- Medically-attended adverse events (MAAEs) from the day of vaccination until 6 months after the last vaccination
 
- Lab parameters: biochemistry and haematology at 1 month visit.
 |

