## **4. Study Design**

### **4.1. Overall Design**

This is a randomized, non-blinded, controlled, adaptive, multicenter, Phase II study in subjects aged more than 18 years and in good health or stable clinical situation that have received a previous single dose of VAXZEVRIA.

This is a phase 2 adaptive trial developed for evaluating the immunogenicity of a dose of COMIRNATY after a previous single dose with VAXZEVRIA. A stratification will be made for the following factors: site of vaccination, sex and age. This protocol allows to test the immunogenicity and safety of a heterologous vaccination strategy after a single dose of VAXZEVRIA.

Subjects will be randomized to immediately receive or not dose of COMIRNATY in a proportion of 2:1.

If primary analysis at 14 days confirms the starting hypothesis, subjects randomized to no vaccination will be considered for administration of one dose of COMINARTY at day 28th according to Public Health Department of the Ministry of Health recommendations on heterologous vaccination. If vaccinated, subjects will be followed at the time points defined in the flowchart.

In case the primary analysis does not confirm the starting hypothesis, subject will be followed without administration of COMINARTY.

In case Public Health Department gave instructions to give the second dose of VAXZEVRIA to those subjects having received the first dose, subject will be followed as indicated in flowchart of Group 2.

Other heterologous vaccination strategies could be incorporated if deemed necessary for public health reasons. This could include the use of different boost strategies including those already marketed vaccines for comparative assessment of their safety and efficacy on SARS-CoV-2 and its variants.

The different intervention arms planned (and its corresponding control arm) can be carried-out in different trial sites, thus not all trial sites must participate in all arms.

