#### **6.1.2. Control arm:**

The control arm (Group 2) will have no vaccine administration. If primary analysis at 14 days confirms the starting hypothesis, subjects randomized to no vaccination will be considered for administration of one dose of COMINARTY at day 28th according to Public Health Department of the Ministry of Health recommendations on heterologous vaccination. If vaccinated, subjects will be followed at the time points defined in the flowchart (Group 2).

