### **9.3.5. Safety analyses**

Safety endpoints include serious adverse events (SAEs) leading to study treatment discontinuation and death. SAEs will be coded using the current version of the Medical Dictionary for Regulatory Activities (MedDRA). SAEs leading to study treatment discontinuation and death will be summarized with absolute and relative frequencies (%) with 95% confidence intervals (CIs). More details on the statistical analysis will be provided in the SAP.

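### Section 8.4.1 closes the pre-existing-condition window at first vaccination rather than at randomization, so control-arm events, mainly non-serious ones, can be filed as medical history

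*Protocol*

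**What the plan says.** Section 8.4.1 sets the cut-off: "Any clinically relevant event that occurs between signing of the ICF and the first vaccination will be collected and reported as pre-existing medical condition". It makes no separate provision for Group 2.

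On that group, Section 6.1.2 says: "The control arm (Group 2) will have no vaccine administration". If the Day 14 analysis confirms the hypothesis, "subjects randomized to no vaccination will be considered for administration of one dose of COMINARTY at day 28", subject to public health recommendations. Otherwise Section 4.1 says: "In case the primary analysis does not confirm the starting hypothesis, subject will be followed without administration of COMINARTY".

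Other text runs on a different clock. The first bullet of 8.4.1 reads: "All AEs and SAEs will be collected from the signing of the informed consent form (ICF) until the follow-up visit". Its last bullet has every event that meets the SAE definition reported as an SAE. Table 3.1 lists as an endpoint "Serious adverse events (SAEs) throughout the study (from randomization until end of the study"). The Group 2 flowchart in Section 1.2 marks the SAE and MAAE rows at Visit 1.

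The exceptions under Table 8.4.1 remove from immediate SAE reporting "pre-existing diseases or present conditions detected prior to start of study drug administration and which do not worsen".

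Section 9.3.5 says: "Safety endpoints include serious adverse events (SAEs) leading to study treatment discontinuation and death".

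**The concern.** The pre-existing-condition rule exists to separate what a participant brought into the trial from what happened during it. In a randomized comparison that line belongs at randomization, because from then on the two arms should be observed in the same way. Here the line is drawn at an event that one arm has on Day 0 and the other has four weeks later or not at all. Background events would count as adverse events in the vaccinated arm and could be entered as history in the control arm.

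Safety is a primary objective, and the monitoring committee may recommend stopping for harm (Section 9.4). The period before any crossover is the only one with a randomized unvaccinated comparison. A labelling rule that differs by arm pushes that comparison in one direction: any excess in Group 1 looks larger than it is. The SAE exception is also tied to the start of study drug, so for undosed controls it is unclear when the exception stops applying.

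**Working it through.** The protocol gives no figure on this point, so the check is mainly a comparison of texts.

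**1. What first vaccination means.** Inclusion criterion 1 places the VAXZEVRIA dose 8 to 12 weeks before screening, and consent is taken at screening. VAXZEVRIA therefore cannot close a window that opens at consent. The only candidate is the trial dose of COMIRNATY.

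**2. When the window closes in each arm.**

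| Arm | Trial dose | Window closes |
|---|---|---|
| Group 1 | Visit 1, Day 0 | Day 0 |
| Group 2, crossed over | Visit 4, nominal Day 28 | Day 28 |
| Group 2, not crossed over | none | no defined end |

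Crossover depends on the Day 14 analysis. When a control has an event on Day 10, the site cannot know whether there will ever be a first vaccination. Section 9.3.1 places baseline at the Day 1 visit, so the cut-off does not match the protocol's own baseline for Group 2 either.

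**3. Which events other text protects.**

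- *SAEs.* Protected by the first and last bullets of 8.4.1, by the Table 3.1 window and by the Visit 1 flowchart mark. The exception under Table 8.4.1 works against this.
- *MAAEs.* Partly protected. The Group 2 flowchart marks them at Visit 1, but the endpoint text in the synopsis and Table 3.1 starts at vaccination.
- *Other non-serious events.* Weakly protected. The first bullet of 8.4.1 covers them. However, the crossover flowchart marks the solicited and unsolicited rows only at Visit 4, and the Visit 2 and 3 questions in Section 8 ask about the time since the vaccine dose, which controls have not had.

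**4. Who is analysed.** The safety set in Section 9.2 takes participants exposed to a study intervention. If that means the vaccine, undosed controls are not in it, whatever label their events carry. This is a separate cause that acts in the same direction.

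**5. Size of the window** (arm sizes from the synopsis).

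- Controls to Day 28: 200 × 28 = 5,600 person-days, or 5,600 / 365.25 = 15.3 person-years.
- Group 1 over the same days: 400 × 28 = 11,200 person-days, or 30.7 person-years, with events counted from Day 0.
- Controls to Day 360 if never dosed and read literally: 200 × 360 = 72,000 person-days, or 197.1 person-years.

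These are observation times, not event counts. A count needs a background rate that the protocol does not give.

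**6. Section 9.3.5.** Section 7.1 says discontinuation of study intervention is not applicable, because the intervention is one dose. The category of SAEs leading to treatment discontinuation is therefore empty by the protocol's own terms. Table 3.1 lists five safety endpoints: solicited events, unsolicited events, SAEs, MAAEs and laboratory parameters.

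**The case against.** A reader might infer that every control-arm event to Day 28 or study end vanishes from the safety data. The text does not support that. The bullet covers only clinically relevant events and says that they are collected and reported, so they stay on record under the wrong heading. SAEs have explicit contrary text in the same section. A Group 2 that does not cross over follows the Group 1 visits, where events are asked about.

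A reader might also put a number on the loss. At an assumed 5% to 20% of controls with an event by Day 28, 200 × 0.05 = 10 to 200 × 0.20 = 40 participants would be involved. Those rates are not in the protocol, and taking the control count to zero needs the extreme reading rejected above. The solicited and unsolicited endpoints are defined after vaccination, so control events before a dose fall outside them whatever 8.4.1 says. The protocol plans no test of adverse events between arms, and causality is judged event by event.

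On reporting, a new serious event in a control meets the SAE definition and must be sent within 24 hours. The exception is limited to conditions that do not worsen. The text therefore does not show that control-arm SAEs would go unreported.

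On 9.3.5, the sentence says include and the section leaves detail to the SAP, so it does not replace Table 3.1.

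All of this limits the point. It does not remove the contradiction: a site cannot file one event both as an adverse event and as a pre-existing condition, and the protocol does not say which instruction prevails. Safety data are to be listed by treatment arm, so readers will compare arms even without a test.

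**Conclusion.** The point holds as a misplaced anchor and an internal contradiction. From randomization to Day 28, or without a defined end if there is no crossover, clinically relevant control-arm events can be recorded as medical history while the same events in Group 1 count as adverse events. Non-serious events are the most exposed. MAAEs are exposed through their conflicting windows. For SAEs the weight of the text favours reporting, but the exception under Table 8.4.1 leaves expedited reporting of control-arm events ambiguous.

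Any comparison of the arms would be biased toward more events in the vaccinated arm. The number of affected controls is not quantified. The conclusion rests on reading first vaccination as the trial dose, which the eligibility timing requires. The wording in 9.3.5 is a secondary error.

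**What to change.** 1. In Section 8.4.1, replace the first vaccination with randomization (Visit 1) as the end of the pre-existing-condition window, for both groups.
2. Reconcile the exception under Table 8.4.1 with the same anchor and with the last bullet of 8.4.1, so that sites have one reading for undosed controls.
3. Reconcile the MAAE window in the synopsis and Table 3.1 with the Visit 1 mark in the Group 2 flowchart.
4. Reword the safety set in Section 9.2 so that undosed controls are included.
5. Summarise at least SAEs and MAAEs by randomized arm from randomization to Day 28.
6. In Section 9.3.5, remove the reference to treatment discontinuation and point to the Table 3.1 safety endpoints.

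The cost is a wording amendment and a note to sites. No visits or tests are added, since the flowchart already marks SAEs and MAAEs from Visit 1. A Day 0 to 28 table of solicited and unsolicited events by arm is not part of this fix. It would need new endpoint windows and diary collection in controls, which is more than a wording change.

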#### **8.4.2. Method of detecting AEs and SAEs**

- Care will be taken to not introduce bias when detecting AEs and/or SAEs. Open-ended and non-leading verbal questioning of the participant is the preferred method to inquire about AE occurrences.

#### **8.4.3. Assessment of AEs and SAEs**

##### **Seriousness**

For any adverse event, the investigator must determine whether the event meets one or more of the seriousness criteria described in Table 8.

**Table 8. AE severity scale (**

|                                       |                                                                                                                                            |
|---------------------------------------|--------------------------------------------------------------------------------------------------------------------------------------------|
| Grade 1
(Mild)             | Mild or transient discomfort, without limitation of normal daily activities; no medical intervention or corrective treatment required.     |
| Grade 2
(Moderate)         | Mild to moderate limitation of normal daily activities; minimal medical intervention or corrective treatment required.                     |
| Grade 3
(Severe)           | Marked limitation of normal daily activities; medical intervention and corrective treatment required, possible hospitalization.            |
| Grade 4
(Life-threatening) | Severe limitation of normal daily activities; medical intervention and corrective treatment required, almost always in a hospital setting. |

### Causality

The investigator must assess the causality of all AEs/SAEs in relation to IMP, research procedures, and concomitant medications, using the following guidelines:

- **Related** – The AE is known to occur with the study intervention, there is a reasonable possibility that the study intervention caused the AE, or there is a temporal relationship between the study intervention and event. Reasonable possibility means that there is evidence to suggest a causal relationship between the study intervention and the AE.
- **Not Related** – There is not a reasonable possibility that the administration of the study intervention caused the event, there is no temporal relationship between the study intervention and event onset, or an alternate aetiology has been established.

All AEs/SAEs for which the investigator or the sponsor considers a causal relationship to be a reasonable possibility are considered suspected SARs.

Assessment on expectedness is usually done by the sponsor.

## 8.5. Regulatory reporting requirements for serious adverse events

The sponsor assumes responsibility of reporting AEs and SAEs to the corresponding regulatory authorities. At the same time, the sponsor must report to the investigator all suspected unexpected serious adverse reactions, known as SUSARs. SUSARs must be reported as well to the corresponding IEC/IRB unless otherwise indicated by institution.

## 9. Statistical Considerations

The statistical analysis plan (SAP) will be finalized prior to database lock and it will include a more technical and detailed description of the statistical analyses described in this section. This section is a summary of the planned statistical analyses of the most important endpoints including primary and key secondary endpoints.

### 9.1. Statistical Hypotheses

The efficacy hypothesis is:

$H_0: G(Y1) / G(Y2) = 1$  versus  $H1: G(Y1) / G(Y2) > 1$

With definition:

$G(Y1)$  is the titer of antibodies binding to the SARS-CoV-2 S protein at 14th day after a dose of COMIRNATY in subjects that received a prior single dose of VAXZEVRIA.

$G(Y2)$  is the titer of antibodies binding to the SARS-CoV-2 S protein at 14th day in subjects not receiving the COMIRNATY dose at randomization.

The antibodies binding to the SARS-CoV-2 S protein will be measured as lognormal distribution.

